#### Eating Behavior Documentation and Analysis

The subjects documented all their caloric intakes (food selection, amount and time of each meal) for 14 consecutive days during the run-in period, during both TRE intervention phases, and for 3 consecutive days in the washout phase. The participants documented their food intakes either in form of paper-based handwritten food diaries or using the Fddb Extender app that is a free smartphone application to keep an electronic food diary (https://fddb.info/) (69). The study subjects were instructed to weigh all food whenever possible and to supply information on food details (e.g., brand names) and mealtimes. When weighing was not possible (e.g., when dining out), they were instructed to record their food intake in household measures (cups, glasses, teaspoon, etc.). Subjects who document their nutrition with the Fddb extender app obtained detailed introduction on how to use the app at their screening visit. Subjects who were not familiar with using a smartphone completed paper-based handwritten dietary records, which were later incorporated in the Fddb app by a study assistant.

Energy intake and diet composition were assessed using the free FDDB food database (Fddb Internetportale GmbH, https://fddb.info/) for both the paper- and app-recorded intake to ensure comparability. Dietary records from each condition were analyzed for total energy intake and macronutrient composition. The reported time of all food intakes was used to monitor participant adherence to the designated eating window. To determine the daily eating window, the time interval between the first and last caloric intake of the day was calculated. These self-reported time windows were verified by examining the pattern of glucose excursions using the 24-h CGM data.

At the end of the study, each participant received individual nutritional counseling with an aim to reduce body weight based on the recommendations of the German Nutrition Society (DGE) guidelines and adjusted to their eating behavior and health condition (e.g., pre-diabetes).

#### Continuous Glucose Monitoring

The study participants were fitted with a Freestyle Libre 2 CGM system (Abbott) during the run-in period and during both dietary intervention phases. CGM measured interstitial fluid glucose every 15 min for 14 consecutive days, using a subcutaneous sensor placed in the upper arm area. Each participant was educated on how to wirelessly scan the Freestyle Libre 2 (Abbott) sensor with the corresponding FreeStyle Libre 2 (Abbott) portable reader. At the next examination visit, the glucose data were saved in the study database. Mean daily glucose level, mean amplitude of glycemic excursions (MAGEs), mean of daily differences (MODDs), and continuous overall net glycemic action (CONGA) were analyzed (70).

#### OGTT and Blood Sample Analyses

At screening examination and visits 1–4, an OGTT was performed starting at 09:30 h after overnight fast. Following the insertion of an intravenous catheter and collection of fasting blood sample (−5 min), the participants ingested a drink containing a 75 g load of glucose within a 5 min time frame. Blood samples were drawn at 30, 60, 90, 120 and 180 min of the test using EDTA-containing and serum monovettes (Sarstedt, Germany). For the analysis of incretins, 10 μg/ml aprotinin (Roth, Germany) and 50 μM DPP4 inhibitor (Merck Millipore, Darmstadt, Germany) were additionally added to the blood samples. EDTA monovettes were centrifuged directly, whereas the serum monovette was kept for 10 min at room temperature to clot before centrifugation at 1,800 × g for 10 min at 4°C. The serum and plasma samples were stored at −80°C until analysis.

Measurement of routine laboratory parameters, such as aspartate aminotransferase (ASAT), alanine aminotransferase (ALAT), gamma-glutamyl transferase (GGT), creatinine, urea, uric acid, C-reactive protein (CRP), glucose, glycated hemoglobin (HbA1c), and blood lipids (total cholesterol, high density lipoprotein (HDL)-cholesterol, triglycerides (TG), and non-esterified fatty acids (NEFAs) were performed using ABX Pentra (Horiba). LDL cholesterol was determined using the Friedewald equation (71).

Measurement of metabolic and inflammatory biomarkers in the plasma and serum samples was performed by commercial Enzyme-linked Immunosorbent Assays (ELISA) or multiplex assays according to the recommendations of the manufacturer. Biomarkers included but were not limited to hormones related to glucose metabolism (insulin, C-peptide, glucagon, glucagon-like peptide-1, and glucose-dependent insulinotropic polypeptide), hormones of appetite regulation (peptide YY and ghrelin), adipokines (adiponectin and leptin), and inflammatory markers (interleukine 6, tumor necrosis factor alpha, and monocyte chemoattractant protein 1).

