### eTRE and lTRE Interventions

Before and after each intervention period (eTRE and lTRE), the participants visited the examination center where anthropometrical measurements, fasting blood sampling, and OGTT were performed after overnight fast, and PSQI sleep questionnaire were completed (visits 1–4, Figure 1). Subcutaneous adipose tissue (SAT) biopsies were taken after both intervention periods (visits 2 and 4). At visits 1 and 3, the CGM sensor and ActiGraph were fixed on the body, and nutritional consulting was performed by the dietician who explained eating behavior during the TRE intervention.

The participants were instructed to consume their habitual food between 8:00 and 16:00 h during the early TRE intervention phase and between 13:00 and 21:00 h during the late TRE intervention period to achieve a daily eating window of 8 h and fasting window of 16 h (Figure 1). The subjects were asked to consume their usual kind and amount of food within the 8 h eating window but were free to divide their food intake into as many meals or snacks as desired. For guidance, the participants received a copy of their individual food records and daily caloric intakes made in the run-in phase. Outside the eating window, the participants were allowed to consume water and non-caloric drinks e.g., tea and black coffee without sugar and milk, and, in limited amounts, very low-caloric diet sodas, mints, or chewing gum with sweeteners as a tool that may increase compliance. Telephone calls in the middle of each intervention and the run-in phase (7 days after visiting the examination center) were conducted in order to promote adherence to the assigned program and answer questions. Again, for the 14 consecutive days of the TRE intervention, the subjects documented eating behavior, wore the CGM sensor and ActiGraph device, and completed sleep diaries and weight protocols (Figure 1; Table 1).

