#### Questionnaires and Decision Behavior Tests

The chronotypes of the subjects were assessed using the Munich Chronotype Questionnaire (MCTQ) and the Horne-ÖstbergMorningness-Eveningness Questionnaire (MEQ).

Satiety and hunger scores were assessed using Visual Analog Scale (VAS) for (1) desire to eat, (2) hunger, (3) satiety, and (4) capacity to eat, as described previously (21). VAS surveys were completed once in the morning at 8:00 h and once in the evening at 20:00 h on the last day of each intervention (the day before visits 2 and 4).

Social and economic decision behaviors were assessed by computer tests together with the Barratt Impulsiveness Scale and the UCLA Loneliness Scale in cooperation with [name] (Dept. Decision Neuroscience and Nutrition, German Institute of Human Nutrition).

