### Expected Findings

The study hypothesis is that both interventions will improve glycemic control, lipid metabolism, inflammation, and sleep quality because of reduced eating time while minimizing weight loss as effectively as possible. In detail, we expect an improvement in glucose tolerance, insulin sensitivity, and, possibly, beta-cell function, and a decrease in postprandial and daily mean glucose levels. Moreover, we expect that participants with impaired fasting glucose or impaired glucose tolerance will improve their glycemic status more effectively than people with normal glucose tolerance. We also expect a decline in blood pressure, blood triglycerides, total and LDL cholesterol, and possibly in sleep quality upon both eTRE and lTRE interventions. Furthermore, based on previous observations concerning meal timing and TRE, we hypothesize that the restriction of food intake at the beginning of the day (eTRE) will show more beneficial metabolic effects compared with the food intake restriction at the end of the day (lTRE), which might be associated with different molecular signatures in the fasting adipose tissue. We expect that genes and pathways involved in glucose and lipid metabolism, inflammation, oxidative stress, and autophagy, as well as clock genes, will be affected by meal timing. Finally, we suppose that eTRE vs. lTRE will shift the internal circadian time assessed by the BodyTime assay in opposite directions.

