The same limitation has to be considered for the analysis of strongly circadian regulated clinical outcomes. However, most metabolic measures planned in the protocol (such as glucose, insulin, and incretins) are relatively stable in the fasting state and are much stronger affected by the meal intake than by the endogenous circadian rhythm. Such endogenous circadian rhythms usually show a relatively small amplitude and could be observed mostly in carefully controlled constant routine experiments. Therefore, it cannot be expected that the timing of food intake on the day before will meaningfully affect metabolic parameters in the morning after the overnight fast because of the phase shift in rhythmicity.

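### With the OGTT fixed at 09:30, the primary outcome follows a fast about 5 h longer under eTRE than under lTRE, so a Matsuda difference cannot be ascribed to eating time apart from acute fast length

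*Protocol article*

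**What the plan says.** - **Test time.** The section OGTT and Blood Sample Analyses fixes one clock time for all visits: "an OGTT was performed starting at 09:30 h after overnight fast". No fasting length is given.
- **Eating windows.** The section eTRE and lTRE Interventions has participants eat "between 8:00 and 16:00 h during the early TRE intervention phase and between 13:00 and 21:00 h during the late TRE intervention period". Study Design describes both regimens as giving 16 h of fasting per day.
- **Day before the test.** Questionnaires and Decision Behavior Tests identifies the last day of each intervention with the day before visits 2 and 4. The assigned window therefore governs the last meal before each post-intervention OGTT.
- **Outcome and model.** The primary outcome is the Matsuda index from the OGTT (Primary and Secondary Outcomes). The mixed model has treatment, period and residual effect as fixed factors and participant as random factor (Statistical Analysis).
- **Defence offered.** The Discussion names sampling at a single morning time point as a main limitation. It then says that "it cannot be expected that the timing of food intake on the day before will meaningfully affect metabolic parameters in the morning", and the rest of that sentence limits the claim to a shift of rhythm phase. Elsewhere the Discussion credits the run-in and the baseline recording with removing confounding.

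**The concern.** The trial aims to say whether eTRE or lTRE is the better regimen for cardiometabolic health, with calorie intake and weight held as constant as possible so that timing can be isolated. If every test under one regimen follows a longer fast, a difference in Matsuda has two explanations that the data cannot separate. One is two weeks of early versus late eating. The other is the number of hours since the last meal on the test morning. The fasting blood markers and the adipose biopsy, taken at the same visits, carry the same ambiguity. The article never mentions unequal fast length, so a reader would take the Matsuda contrast as an effect of eating time alone.

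**Working it through.** **1. The plan's own figures.** Both windows last 8 h, so each day contains 24 − 8 = 16 h of fasting, as stated. The power statement also reproduces. For a two-sided paired t-test with n = 30 and effect size 0.53, the noncentrality is 0.53 × √30 = 2.90 with 29 degrees of freedom, and power is 0.801. Neither figure is in dispute.

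**2. Fast before the OGTT**, with last intake at window close. Fast = (24:00 − window close) + 09:30.

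| | Window closes | Hours to midnight | Plus 9.5 h |
|---|---|---|---|
| eTRE | 16:00 | 8.0 | **17.5 h** |
| lTRE | 21:00 | 3.0 | **12.5 h** |

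The difference is 5.0 h. For the blood sample 5 minutes before the load, the fasts are 17.4 h and 12.4 h. Neither test follows the 16 h fast that describes the daily pattern.

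**3. How firm the gap is.** These are minimum fasts for an adherent woman, since an earlier last intake lengthens either one. The gap equals the last lTRE intake time minus the last eTRE intake time. As the latter is 16:00 at the latest, the eTRE fast is longer for any adherent woman who eats after 16:00 under lTRE. The realised gap varies around 5 h, but its direction is set by assignment.

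**4. What might remove it.**
- *Cross-over:* each woman is her own control, but she carries the longer fast in her eTRE period whichever sequence she is in.
- *Period and residual-effect terms:* these describe order and carry-over. The gap goes with treatment.
- *Baselines:* visits 1 and 3 follow habitual eating. If the habitual fast is h hours at both, the difference in changes is (17.5 − h) − (12.5 − h) = 5.0 h.
- *Sample size:* this reduces random error, not a systematic difference.

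**5. The alternative timing.** Equal 16 h fasts would place the test at 16:00 + 16 h = 08:00 under eTRE and 21:00 + 16 h = 13:00 under lTRE. Clock time would then differ with treatment instead.

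**6. Sensitivity of the test (assumption only).** The documents give no effect of fast length on Matsuda. Suppose that the gap alone shifts the paired difference by b standard deviations. The middle row has no other treatment effect. The last row has a true effect of 0.53, with the shift acting against it.

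| b | 0.1 | 0.2 | 0.3 | 0.4 |
|---|---|---|---|---|
| Probability of p < 0.05 | 8.3% | 18.5% | 35.5% | 56.3% |
| Power (80% if b = 0) | 62% | 42% | 23% | 11% |

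The table shows what a shift of given size would do. It is not evidence that such a shift exists.

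**The case against.** **Fixed clock time is a reasonable choice.** Step 5 shows that equalising the fast would only move the problem to time of day. A longer fast by morning is also what early eating entails, so the comparison is valid for the regimens as assigned. Both points stand. The remaining issue is interpretation: the article does not say that the longer fast is part of the contrast.

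**The Discussion already covers timing.** It discloses the single time point and says that glucose, insulin and incretins are fairly stable in the fasting state, which bears on fast length. This stands in part. The remark is general and does not compare 12.5 h with 17.5 h, and the conclusion drawn is limited to phase shift. The same paragraph holds that these measures respond far more to meals than to the endogenous rhythm, which makes time since the last meal more relevant.

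**Stronger readings that the documents do not support.**
- A reader might infer that the Discussion contradicts the prediction that "eTRE vs. lTRE will shift the internal circadian time assessed by the BodyTime assay in opposite directions", or the sizing on morning versus evening meal tests. It does not. A phase shift may occur and still matter little at a fixed morning test, and the sizing data come from tests at different clock times. This is tension only.
- A reader might see the same flaw in the visual analogue scales, since "VAS surveys were completed once in the morning at 8:00 h and once in the evening at 20:00 h". Hunger at a fixed hour, including after the eTRE window has closed, is a direct consequence of the regimen and a legitimate outcome.
- A reader might want to adjust for hours since last intake and for BodyTime internal time. Scheduled diaries cover only the first two of the four run-in weeks and three unspecified washout days, so last intake before visits 1 and 3 need not be recorded. At visits 2 and 4, fast length is nearly collinear with treatment. Both covariates are also consequences of treatment.

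**Conclusion.** The point holds as a limit on what the primary result can mean. A woman who eats until her window closes is tested after about 17.5 h of fasting under eTRE and 12.5 h under lTRE. This 5 h gap is aligned with treatment, and no planned design or model feature removes it. The contrast is valid for the two regimens as assigned and tested at 09:30. It does not support attributing a difference in Matsuda, fasting markers or adipose transcriptome to eating time independent of acute fast length.

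This rests on adherence to the window on the day before visits 2 and 4, and on there being no standardised last meal before the test; the article describes none. A reader might go further and infer that the Matsuda comparison is biased by a known amount, for instance by reading the 5 h as a 40% difference (5 / 12.5). That percentage concerns hours, not Matsuda, and the documents give neither size nor direction for the effect.

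**What to change.** 1. **State the fasts and correct the Discussion.** Give 17.5 h and 12.5 h as the minimum fasts before the post-intervention OGTT. Say that the clock time was held constant because equal fasts would have required tests at 08:00 and 13:00. Restrict the statement on prior-day meal timing to phase shift, say that it does not cover fast length, and withdraw the claim that the run-in and baselines remove confounding.
2. **Define the primary contrast.** Suggested wording:

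   > The primary comparison is between eTRE and lTRE as assigned, with the Matsuda index measured at 09:30, including the difference in time since last intake that the regimens produce. Differences in Matsuda, fasting markers or adipose transcriptome will not be attributed to eating time independent of acute fast length.

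3. **Name a key supportive endpoint.** Use 14-day CGM mean daily glucose, which is already a secondary outcome, is collected in both interventions and does not depend on a single fast. Report it beside Matsuda to qualify the conclusion. Do not make agreement a condition for concluding, since that would add a hurdle for which the trial was not sized.

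**Cost.** These are changes to wording and reporting, with no new measurements and no change to test times or sample size. The conclusion becomes more cautious. CGM mean glucose describes glucose level, not insulin sensitivity, so it can support or temper the Matsuda result but not replace it.

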#### Subcutaneous Adipose Tissue Biopsies and Blood Monocyte Collection

Subcutaneous adipose tissue biopsies were collected at visits 2 and 4 at the level of the umbilicus using a well-established technique (72). The skin was anesthetized with 1% lidocaine. A small incision was made, and 1 g of adipose tissue was removed under sterile conditions using a cutting needle biopsy handy (14 G Somatex™, Germany). SAT biopsies were collected immediately before OGTT and frozen in liquid nitrogen until further analyses. An RNA-Seq analysis of the SAT samples was performed to elucidate and compare signaling pathways affected in the adipose tissue by eTRE and lTRE and validated by quantitative real-time PCR.

Peripheral blood mononuclear cells were isolated from fasting EDTA blood using BD Vacutainer® CPTTM with an integrated FICOLL™-gradient (BD Biosciences, East Rutherford, NJ, USA). Blood monocytes were isolated from the peripheral blood mononuclear cell (PBMC) samples using whole-blood CD14 microbeads (Miltenyi Biotec, North Rhine-Westphalia, Germany) as described (73). The PBMC and monocyte samples were stored at −80°C until the analysis of inflammatory gene expression and BodyTime assay for the determination of TRE effects on internal circadian time (74).

#### Actigraphy and Physical Activity Assessment

Twenty-four-hour physical activity was measured with the ActiGraph wGT3X-BT (ActiGraph) activity monitor to ensure that it will stay constant for the whole duration of the study. The participants wore the accelerometer on the wrist of their non-dominant arm for 14 days during the run-in phase and during both TRE interventions simultaneously with CGM and nutrition assessment. The subjects were asked to wear the ActiGraph device day and night and only take it off if taking a bath or swimming. The device contains a wear time sensor to simplify compliance monitoring. Furthermore, the participants documented the times they were not wearing the activity monitor. Individual physical activity levels, energy expenditure, and metabolic equivalent of task (MET) were analyzed with the ActiLife software version 6.13.4 (ActiGraph).

#### Sleep Analysis

Because subjects reported sleep improvement upon the shortening of eating time in the study of Gill et al. (41), we analyzed TRE effects on sleep quality and duration using subjective and objective methods. During the course of each examination day, the participants assessed their sleep quality during the previous 2 weeks by the Pittsburgh Sleep Quality Index (PSQI) (75), which evaluates seven components of sleep architecture, subjective sleep quality, sleep latency, sleep duration, habitual sleep efficiency, sleep disturbances, use of sleeping medication, and daytime dysfunction. The objective analysis of sleep was performed using ActiGraph wGT3X-BT devices following the assessment of sleep latency, total sleep time, sleep efficiency, and sleep fragmentation index by the ActiLife software as described (76). Sleep timing for this analysis was obtained from the sleep diaries where the subjects documented their bedtime and wake-up time for 14 days during the wearing of ActiGraph device, and added manually.

#### Questionnaires and Decision Behavior Tests

The chronotypes of the subjects were assessed using the Munich Chronotype Questionnaire (MCTQ) and the Horne-ÖstbergMorningness-Eveningness Questionnaire (MEQ).

Satiety and hunger scores were assessed using Visual Analog Scale (VAS) for (1) desire to eat, (2) hunger, (3) satiety, and (4) capacity to eat, as described previously (21). VAS surveys were completed once in the morning at 8:00 h and once in the evening at 20:00 h on the last day of each intervention (the day before visits 2 and 4).

Social and economic decision behaviors were assessed by computer tests together with the Barratt Impulsiveness Scale and the UCLA Loneliness Scale in cooperation with [name] (Dept. Decision Neuroscience and Nutrition, German Institute of Human Nutrition).

### Primary and Secondary Outcomes

The primary outcome was the insulin sensitivity assessed using Matsuda index in OGTT (77). Secondary outcomes included body weight, BMI and body fat content, fasting glucose, homeostasis model assessment of insulin resistance (HOMA-IR), indices of insulin secretion and beta-cell function assessed in OGTT, mean daily glucose and daily glycemic variation indices assessed in CGM, levels of hormones related to glucose metabolism, hormones of appetite regulation, adipokines and inflammatory markers, blood lipid and liver enzyme levels, systolic and diastolic blood pressures, satiety and hunger scores, sleep quality and duration, physical activity, social and economic decision behaviors, dietary calorie intake, composition, timing, and eating window duration. The main exploratory outcome was the activity of signaling pathways and expression of metabolic and inflammatory genes in adipose tissue and blood monocytes.

